#### Preventive care receipt

##### Assessment

Clients will be asked whether, during an appointment with the service a clinician asked: if they smoke any tobacco products; how many vegetables and fruit they eat; how much alcohol they drink; and how much physical activity they do (yes, no, don't know).

##### Brief advice

Clients identified as being 'at risk' for any risk will be asked whether a clinician advised them to: quit smoking, or advised about Nicotine Replacement Therapy [72]; eat more fruit, or vegetables [58]; reduce how much alcohol they consume [69], and do more physical activity [73] (yes, no, don't know).

##### Referral

'At risk' clients will be asked whether a clinician asked if their general practitioner/Aboriginal Medical Service provider could be informed of the consultation; offered to arrange a referral to the Quitline for smoking, or the Get Healthy Information and Coaching service for inadequate fruit and vegetable consumption and/or physical inactivity; or advised them to visit their general practitioner/Aboriginal Medical Service provider (yes, no, don't know) for risky alcohol use.

##### Acceptability of preventive care delivery

Clients will be asked if clinician provision of risk assessment, and for 'at risk' clients, brief advice and referral, was acceptable for each risk individually and for all risks simultaneously (strongly disagree, disagree, unsure, agree, strongly agree).

##### Clinician characteristics and risk status

Consenting clinicians will be asked to report: their age (< 40, 40-49, 50-59, 60+); Aboriginal or Torres Strait Islander Origin status (yes, no); current employment status (full time, part time, casual, other); number of years in their discipline (< 1, 1-2, 3-4, 5-9, 10+), and years working in community health (< 1, 1-2, 3-4, 5-9, 10+). Clinicians will be asked to report their risk status for each of the four risks in the past month, using the same questions and response categories as previously described for clients.

The following clinician information will be obtained from health service records: position, team, professional type, postcode of service, and gender.

#### Preventive care delivery

##### Assessment

Clinicians will be asked to estimate the proportion of their new adult clients from the previous two months for whom they had assessed smoking status, fruit and vegetable intake, alcohol consumption, and current physical activity status (for each risk: 0 to 100%, don't know).

##### Brief advice

In the telephone interview, clinicians will be asked to report on the proportion of 'at risk' clients that they advised: to quit smoking, to eat more fruit and/or vegetables, to reduce alcohol intake, and to increase physical activity levels (for each risk: 0 to 100%, don't know).

##### Referral

Clinicians will be asked to report the proportion of clients for whom they informed the client's general practitioner/Aboriginal Medical Service provider of the client's risk status and care received (0 to 100%, don't know). In addition, clinicians will be asked to report the proportion of clients at risk for smoking, inadequate fruit or vegetable consumption or physical inactivity with whom they spoke to about the recommended telephone service, or their general practitioner/Aboriginal Medical Service provider for risky alcohol use (for each risk: 0 to 100%, don't know).

##### Acceptability of preventive care intervention

To determine acceptability of the intervention, the clinician telephone survey will assess: clinicians perceived barriers to the provision of preventive care for the four individual risks, and the four risks simultaneously; the appropriateness, acceptability and utility of the preventive care elements; and the usefulness of the clinical practice change strategies implemented (strongly agree, agree, unsure, disagree, strongly disagree).

#### Practice change intervention delivery

Data regarding the following measures of clinical practice change intervention delivery will be obtained, including: meetings of advisory groups, number of facility contacts; number of clinicians completing training, provision of performance reports.

#### Community health service characteristics

Data regarding community health facility descriptors for each client will be obtained from health service records regarding: service team name (e.g. social work), group (1, 2, 3) and service type (community nursing, allied health, community child and family health, diabetes services, aged care, and other services).

### Sample size

Assuming a baseline prevalence of 50% for all forms of preventive care delivery (worst case scenario), the study will have 80% power to detect a difference of between 4.7% to 21.8% in the assessment of each health risk between baseline and follow-up for the three groups at the 1% significance level. Power estimates for the provision of brief advice and referral for all four risk behaviours are conservatively based on the expected number of smokers; as smoking is the least prevalent risk behaviour [1]. The sample in the third group of facilities (which has the shortest follow-up period) is expected to include approximately 450 (20%) smokers in the baseline period and 75 smokers during the follow-up period. With a brief advice prevalence of 50% at baseline, the study will have over 80% power to detect a 20.9% improvement in the prevalence of such care (i.e. a change from 50.0% to 70.9%). Similarly, with an estimated prevalence of 50% for offering a referral prior to the intervention, the study will have over 80% power to detect a 20.9% improvement in prevalence of such care (i.e. a change from 50.0% to 70.9%).

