There is limited evidence regarding the provision of preventive care for smoking, poor nutrition, alcohol misuse and physical inactivity risks in community health services in Australia and elsewhere [27,32-34]. In a study of three Australian community health teams, Laws et al (2009) found the mean proportion of clients interested in changing their behaviour who reported receiving brief advice or referral regarding these risks ranged between 43-66% [27]. Another Australian study [35] reported low levels of brief advice ranging between 2% and 3% for these four risks. One international study has also reported low levels of assessment (34%), brief advice (46%) and follow-up (0%) for smoking [34]; and another found similarly low levels for smoking assessment (12%) and brief advice (10%), and physical activity brief advice (15%) [33]. Such data suggest that the delivery of preventive care is less than optimal and that the intended clinical and population health benefits of such care are currently unrealised.

The authors located few controlled studies designed to increase the provision of any form of preventive care in community health settings [34-36]. The identified studies were undertaken across one home health care agency [34], 12 Aboriginal community health centres [35], and 42 pre-natal care clinics [36]. The interventions involved one [34], three [36], or six [35] practice change strategies, and reported significant improvements for at least one outcome based either on a medical record audit [35], or client [36] or clinician self-report [34,36]. One study reported the provision of brief advice only [35], while the other two both reported on assessment, brief advice and follow-up. None of these studies reported referral to another service. Two of the studies reported a significant increase in the prevalence of care at follow-up compared to baseline [34] or a control group [35], with a 41% increase for risk assessment [34], increases ranging from 3% to 40% for brief advice [34,35], and an increase of 17% for follow-up [34]. The remaining study reported significant increases in mean scores for assessment, brief advice and follow-up [36].

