#### Clients

All adult clients who have at least one visit to a community health facility for the above types of services within the prior two weeks, and who meet the following inclusion criteria will be eligible to participate in the data collection: over 18 years of age; speak English; mentally and physically capable of completing an interview; not determined by clinician discretion as inappropriate to contact; not involved in another community health care focused survey; and not living in aged care facilities or gaol.

Each week 20 eligible clients who have not previously participated in the study will be randomly selected from the electronic medical records of each of the three groups of facilities (60 clients per week in total). Selected clients will be mailed an information letter then contacted by phone and asked to participate in a telephone interview. As indicated in Figure 1, the three groups will have different numbers of clients participating in the surveys in the baseline and follow-up periods due to the staggered multiple baseline design. The study is anticipated to recruit 750, 1500 and 2250 clients in the baseline period for groups 1, 2 and 3 respectively, and 1875, 1125 and 375 clients in the follow-up period for these groups.

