### Comparison sites

Prior to the implementation of the intervention in each group of facilities, usual preventive care practice change strategies will be utilised in the comparison sites. Some intervention strategies will be applied across the entire district (all groups) but not enacted until each groups' intervention period commences (e.g. the decision on the model of preventive care, and the changes to the electronic records and policy). While some strategies will only be implemented during the intervention period (such as educational outreach visits and academic detailing; and community promotion), some clinical practice change elements will remain after the research project concludes to increase the sustainability of clinician provision of preventive care (e.g. leadership and consensus processes, organisational systems change, and audit and feedback).

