#### Preventive care delivery

##### Client data

For each outcome, evaluation of intervention effectiveness will involve fitting a segmented logistic regression model, including separate intercepts and slopes at baseline, during the intervention and at follow-up (the three "segments") [74,75]. A statistically significant coefficient for the intercept and/or slope during the intervention or follow-up will indicate a change in the outcome measure following the intervention for each group. Standard errors of coefficients, and hence p-values and confidence intervals, will be estimated using bootstrapping [76]. In the first set of models the outcome of interest will assess client reported assessment of risk behaviour. The second set of models will be restricted to those subjects who report a risk behaviour, with separate models assessing whether or not the community health clinician provided brief advice, or offered a referral.

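### The 80% power and the 'worst case' 50% rate belong to a two-proportion test, not to the planned segmented bootstrap model, which can also break down in group 1 if usual-care advice is as low as 2-3%

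*Protocol article*

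**What the plan says.** The Sample size section begins "Assuming a baseline prevalence of 50% for all forms of preventive care delivery (worst case scenario"), and sets its assessment comparison "between baseline and follow-up for the three groups at the 1% significance level". For brief advice and for referral it uses group 3 smokers, "approximately 450 (20%) smokers in the baseline period and 75 smokers during the follow-up period", and concludes that "the study will have over 80% power to detect a 20.9% improvement in the prevalence of such care (i.e. a change from 50.0% to 70.9"%).

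The comparator is the period before each group starts, when "usual preventive care practice change strategies will be utilised in the comparison sites" (Comparison sites). Background gives several usual-care rates. One Australian study "reported low levels of brief advice ranging between 2% and 3% for these four risks"; other brief-advice figures are 10%, 15% and 46%, and a combined figure for advice or referral is 43-66%.

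The Client data section under Statistical analysis does not plan a two-proportion test. It fits a logistic model with its own intercept and slope in each of three periods and reads any significant intercept or slope as a change, group by group. Advice and referral models include only clients with the risk. On inference it states: "Standard errors of coefficients, and hence p-values and confidence intervals, will be estimated using bootstrapping".

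**The concern.** The stated power and the planned test do not belong together. For a difference of two proportions, a rate near 50% is close to the least favourable, so a reader takes 'worst case' to mean that power can only improve elsewhere. That reasoning does not carry over to a model that tests level and slope changes on the log-odds scale. Such a model spends much of its information on slopes, and its coefficients become unstable when a period holds few events.

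The weak spot is group 1, which has the shortest baseline. If usual-care advice were near the bottom of the cited range, many bootstrap resamples would have no or very few baseline events. The resampled coefficient then diverges, and the standard error partly reflects where the fitting algorithm stopped. Smoking and alcohol advice fall under the primary aim, so both the power statement and the validity of those tests are at stake.

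**Working it through.** **1. The protocol's own figure.** Group 3 smokers: 450 baseline, 75 follow-up, 50.0% to 70.9%, two-sided 1% (sidedness is not stated; two-sided reproduces the figure).

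- Pooled rate = (450 × 0.50 + 75 × 0.709)/525 = 0.530.
- Null SE = √[0.530 × 0.470 × (1/450 + 1/75)] = 0.0623.
- Alternative SE = √[0.25/450 + 0.709 × 0.291/75] = 0.0575.
- z = (0.209 − 2.576 × 0.0623)/0.0575 ≈ 0.85, so power = 80.1%.

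For this test the label is nearly right. Power for +20.9 points has its minimum, 79.2%, near a 42% baseline, and is 96.6% at 10% and 99.6% at 3%.

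**2. Expected baseline events.** "The study is anticipated to recruit 750, 1500 and 2250 clients in the baseline period for groups 1, 2 and 3 respectively". Background gives 20% smokers and 13% risky drinkers.

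- Group 1 smokers: 750 × 0.20 = 150; × 2-3% = 3.0 to 4.5 events.
- Group 1 risky drinkers: 750 × 0.13 = 97.5; × 2-3% = 2 to 3 events.
- Group 2 smokers: 300, so 6 to 9 events. Group 3 smokers: 450, so 9 to 13.5.

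At 2%, group 1 smokers have no baseline event with probability 0.98^150 = 4.8% and two or fewer with probability 42%. Given k observed events, a resample contains none with probability (1 − k/150)^150: about 5% for k = 3, 13% for k = 2, 37% for k = 1. In simulation, 12-16% of resamples at 2% and 5-6% at 3% had a segment with no event.

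**3. Simulation of the planned model.** Three segments (50, 50 and 125 weeks in group 1), 20 × 75% = 15 interviews a week times the share at risk, client-level bootstrap, and Wald tests at 1%. A trial counts as a detection if any of the four level or slope changes is significant. The effect is an abrupt, sustained +20.9 points unless noted.

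| Setting | Baseline rate | Bootstrap SE / model SE (level change) | Detected |
|---|---|---|---|
| Group 1 smokers | 50% | 1.02-1.03 | 18-20% |
| Group 1 smokers | 10% | 1.09 | 18% |
| Group 1 smokers | 3% | 2.4-2.9 | 5-8% |
| Group 1 smokers | 2% | 2.4-4.2 | 7-8% |
| Group 2 smokers | 3% | 1.20 | 34.5% |
| Group 2 smokers | 2% | 2.0 | 16% |
| Group 3 smokers | 50% | 1.02 | 31% |
| Group 3 smokers | 2% | 1.16 | 56% |
| Group 1, vegetable advice (86% at risk) | 2% | 1.08 | 94% |
| Group 1, activity advice (72% at risk) | 2% | 1.12 | 84% |
| Group 1, assessment, 12% to 20% | 12% | 1.01 | 34% |

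For group 1 smokers, a plain two-proportion test of baseline against follow-up detects the 20.9-point step in 96-100% of trials. For group 1 risky drinkers at 2%, the SE ratio is 4.7 and 15% of trials have no baseline event.

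**4. No true effect, group 1 smokers.** Four tests at 1% would give about 1 − 0.99^4 = 3.9% by chance; the simulation gives 3.5% at 50%. At 3% it gives about 5%, and at 2% between 11% and 16%.

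**5. Gradual effect.** With a ramp over the intervention year, group 1 smokers are detected in 15% of trials at 50%, 23% at 3% and 30% at 2%.

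**6. What drives the loss at 2%.** On the same data, dropping zero-event resamples raises detection from 7-8% to 30-33%, and percentile intervals raise it to 67%. Model-based Wald tests give only 8%, so exchanging one standard error for another is not enough.

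**The case against.** The strongest reply is that 50% is the right conservative choice for the calculation the Sample size section makes, and that the 2-3% figure is a poor guide to this trial. By the protocol's own account it comes from a medical-record audit in Aboriginal community health centres, whereas the outcome here is client report by telephone. The 43-66% and 46% figures lie close to 50%. At 10%, the next-lowest cited advice rate, the bootstrap behaves well. All of this stands, and it makes the breakdown conditional.

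A reader might infer that low usual care is why group 1 would miss real effects. The simulations do not support that: detection is only about 20% at 50% too, so most of the loss comes from the segmented model, and under a gradual effect power is lowest at 50%. A reader might also extend the breakdown to referral, citing the 0% follow-up rate. Background says the controlled studies, which include the source of that rate, did not report referral to another service; the only cited figure that includes referral is the combined 43-66%.

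It can also be said that rules for failed resamples belong in an analysis plan, which is not shown. That is fair for the detail. But the article itself fixes p-values from bootstrap standard errors of coefficients, and its power statement is for a different test.

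**Conclusion.** The point holds in two parts. First, without condition on the usual-care rate: the 80% power and the 'worst case' label describe a comparison that the Client data section does not plan. Under the planned model, power for the same abrupt rise from 50% is about 20% (group 1 smokers) to 31% (group 3 smokers). Second, conditionally: if usual-care brief advice is near 2-3%, bootstrap standard errors for smoking and alcohol advice break down in group 1 and partly in group 2. In group 1 smokers the level-change standard error is inflated about 2.5 to 4 times, under 10% of abrupt 20.9-point rises are detected, and at 2% false positives exceed the nominal rate.

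The breakdown is mild in group 3, absent at 10% or above, and absent for fruit and vegetable advice, activity advice and assessment. It reaches referral only if referral is similarly rare. The documents do not support saying that the trial's group 1 effects will go undetected because of low usual care.

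Assumptions: 20% smokers and 13% risky drinkers in every group, independent clients, even accrual, no underlying trend, segment terms coded as changes from the previous segment, and diverging fits kept at an iteration limit. Monte Carlo error is about 1 to 3.5 points. The true usual-care rates are unknown.

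**What to change.** In Sample size, limit 'worst case' to the two-proportion comparison. Restate power for brief advice and referral by group, simulated under the planned segmented model over about 2-50% usual care, for both an abrupt and a gradual effect.

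In Client data, prespecify a sparse-event method in place of Wald tests from raw bootstrap standard errors. Options are percentile intervals, or a bootstrap of predicted prevalence differences from a Firth-penalised fit. Resampling should respect facilities, since clients are clustered within them; for the same reason a wholesale switch to ordinary likelihood-ratio tests is not clearly better. Check the false-positive rate of the chosen method in the same simulation: at 50% with no effect, percentile intervals rejected in 5% of trials against 3.5% for the standard-error method.

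The cost is wording, simulation time and standard software, with no extra clients or data. The downsides are slightly shrunk estimates and a less favourable power statement.

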**Figure 1 F1:**
[figure not shown]
**Overview of multiple baseline study showing three phase rollout, intervention periods and outcome measurement**. ^a ^Not randomly allocated. ^b ^Calculated on 50 weeks of data collection per year. ^c ^Based on a 75% consent rate to client survey.

The multiple baseline study design provides a number of advantages that are relevant to the conduct of complex health service research interventions [51,52]. Firstly, the design provides the opportunity for all facilities to participate in the intervention and all clients to receive the intervention (a key motivational requirement for clinician engagement) [52]. Secondly, its sequential implementation allows for any effect of extraneous variables on the outcomes to be monitored [52]. Finally, the design addresses the practical difficulty of recruiting a sufficient number of similar community health facilities, and is more efficient because each group is used as its own control [51,52].

The study is funded by the Hunter Medical Research Institute, and a partnership grant from the National Health and Medical Research Council (application ID: APP1016650) in partnership with the Hunter New England Local Health District. Ethical approval to conduct the study has been obtained from the Hunter New England Human Research Ethics Committee (approval No. 09/06/17/4.03) and University of Newcastle Human Research Ethics Committee (approval No. H-2010-1116).

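### The stated detectable range for risk assessment, 4.7% to 21.8%, does not follow from the protocol's own sample sizes, which give 6.7 to 9.5 points

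*Protocol article*

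**What the plan says.** The Sample size section sets the starting point: "Assuming a baseline prevalence of 50% for all forms of preventive care delivery (worst case scenario"). It then claims that "the study will have 80% power to detect a difference of between 4.7% to 21.8% in the assessment of each health risk", the contrast being "between baseline and follow-up for the three groups at the 1% significance level".

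The numbers behind that contrast are in the Clients section: "750, 1500 and 2250 clients in the baseline period for groups 1, 2 and 3 respectively, and 1875, 1125 and 375 clients", where the second set of three numbers gives the follow-up samples. Non-response is already taken off. The note to Figure 1 reads "Based on a 75% consent rate to client survey", and 20 clients a week × 50 weeks × 0.75 = 750 per group per year.

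For brief advice and referral, the Sample size section uses smokers in group 3 (450 at baseline, 75 at follow-up) and says "the study will have over 80% power to detect a 20.9% improvement in the prevalence of such care", a move from 50.0% to 70.9%.

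**The concern.** The Assessment item under Preventive care receipt is asked of every client. Under Statistical analysis, only the brief advice and referral models are restricted to clients at risk. The full group samples are therefore the denominators for risk assessment, and samples of that size should give a narrow range of detectable differences. The printed range is wide: 21.8 / 4.7 = 4.6.

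The paragraph also disagrees with itself before any calculation. It allows up to 21.8 points for whole groups but 20.9 points for the smokers in group 3, who are one fifth of that group. With the same baseline, power, level and method, a subset cannot detect a smaller difference than the sample that contains it.

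This is the power claim for the first family of primary outcomes. If 4.7 is too low, it promises sensitivity that no group has. If 21.8 is too high, it makes the design look far weaker than it is.

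**Working it through.** **Inputs.** Baseline prevalence p1 = 0.50, power 80% and level 1% (Sample size); group sizes (Clients). Sidedness is not stated, so it is settled by reproducing the protocol's own smoker figure.

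**Formula.** Two independent proportions, pooled variance under the null, with n1 at baseline, n2 at follow-up, p2 = p1 + d and p̄ = (n1·p1 + n2·p2)/(n1 + n2):

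- S0 = √[p̄(1 − p̄)(1/n1 + 1/n2)]
- S1 = √[p1(1 − p1)/n1 + p2(1 − p2)/n2]
- Power = Φ[(d − z·S0)/S1], with z = 2.576 for a two-sided 1% test

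**Step 1: reproduce the protocol's smoker figure.** n1 = 450, n2 = 75, d = 0.209.

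- p̄ = (450 × 0.5 + 75 × 0.709)/525 = 0.530
- S0 = 0.0622 and S1 = 0.0575
- Power = Φ[(0.209 − 2.576 × 0.0622)/0.0575] = Φ(0.846) = 80.1%

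Solving for exactly 80% power gives d = 20.88 points, so the stated 20.9 reproduces. At a two-sided 5% level the answer would be 17.2. The match supports a two-sided 1% test with no inflation for clustering.

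**Step 2: apply the same formula to risk assessment.**

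| Group | Baseline v follow-up | Detectable at 80% power | Power for 4.7 points | Power for 21.8 points |
|---|---|---|---|---|
| 1 | 750 v 1875 | 7.35 | 35% | > 99.9% |
| 2 | 1500 v 1125 | 6.72 | 42% | > 99.9% |
| 3 | 2250 v 375 | 9.49 | 19% | > 99.9% |

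Worked example, group 2 at 4.7 points: S0 = S1 = 0.0197, so power = Φ[(0.047 − 2.576 × 0.0197)/0.0197] = Φ(−0.19) = 42%.

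**Step 3: look for a variant that gives 4.7 to 21.8.**

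| Variant | Range over the three groups (points) |
|---|---|
| Two-sided 1%, continuity correction | 6.8 to 9.6 |
| Two-sided 1%, unpooled variance | 6.7 to 9.4 |
| One-sided 1% | 6.2 to 8.8 |
| Two-sided 5% | 5.5 to 7.8 |
| One-sided 5% | 4.9 to 6.9 |
| Smokers only, by group (two-sided 1%) | 14.9 to 20.9 |

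Pooling all three groups (4500 v 3375) gives 3.9. Pooling groups 1 and 2, or 1 and 3, gives 4.8.

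A common design effect fails as well. To reach 21.8 in group 3 it would have to be about 5.5; to reach 4.7 in group 2 it would have to be about 0.49. Whatever the common inflation, the ratio of largest to smallest detectable difference stays near 9.49/6.72 = 1.4, against the printed 4.6. Single matches to one end turn up only when stated inputs are altered (for example 90% power, or pooled groups with intervention-period data at 5%). No variant tried gave both ends.

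**The case against.** The two ends do not fail equally. Clients come from 56 facilities, and the planned analysis is a segmented logistic regression with separate intercepts and slopes and bootstrapped standard errors. Both features can require a larger difference than a simple before-and-after test, so the figures of 9.5 points and of power above 99.9% at 21.8 are idealised. If 21.8 carries such an allowance, it errs on the cautious side. The conflict with 20.9 also assumes one method for both numbers, which the section does not say. A continuity-corrected smoker comparison in group 3 gives 21.6, so 21.8 may be a smoker figure that strayed into the wrong sentence. Sidedness is inferred, not stated. Finally, the planned confidence intervals will show how precise any null result is, whatever the power statement said.

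Some of this stands. The recomputed figures belong to a simple comparison of independent clients and should be labelled so, and the planned intervals limit the practical harm. It does not rescue the range. The section states no inflation, and its smoker figure reproduces without any. Clustering and extra model terms would move 4.7 further out of reach, and a one-sided 1% test still needs at least 6.2 points. A misplaced smoker figure would still be an error in the sentence on assessment.

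**Conclusion.** The concern holds. Under the stated inputs the detectable differences are 7.3, 6.7 and 9.5 points for groups 1, 2 and 3, not 4.7 to 21.8.

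The lower end is the firmer part: no single group reaches 4.7 points at either the 1% or the 5% level, and at two-sided 1% a true change of that size would be missed more often than found in every group. The upper end is 21.8 / 9.5 = 2.3 times the figure for the least sensitive group, with no stated allowance to account for it.

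The result assumes independent clients, a simple baseline v follow-up comparison, and a two-sided test inferred from the smoker figure. The 20.9% for smokers is consistent with its inputs and is not in question. Recruitment and design are unaffected.

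**What to change.** In the Sample size section, replace the range with per-group figures: 7.3 points (group 1), 6.7 (group 2) and 9.5 (group 3), at 80% power from a 50% baseline. State that these are simple baseline v follow-up comparisons of independent clients at the two-sided 1% level, not the power of the segmented model.

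If 4.7% and 21.8% come from other comparisons, or include an allowance for clustering or for the segmented model, name the comparison, the sidedness and the method behind each so that they can be reproduced.

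The cost is one sentence, with no change to design, sample or analysis.

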## Background

The primary behavioural risks for the most common causes of mortality and morbidity in developed countries are tobacco smoking, poor nutrition, risky alcohol use, and physical inactivity [1-3]. In Australia, 20% of adults are current smokers, 13% consume alcohol at risky levels, 86% have inadequate vegetable consumption, 46% have inadequate fruit consumption, 35% are sedentary, and a further 37% have low levels of physical activity [4]. Furthermore almost all adults (92%) have at least one chronic disease risk, and 44% have three or more such risks [5-7].

Cochrane review evidence [8-12] supports the efficacy of clinician delivery of care to increase: smoking cessation [11,12], the consumption of fruit and vegetables [8], to reduce at-risk alcohol consumption [9], and to increase physical activity [10]. Consistent with such evidence, the routine delivery by health care providers of preventive care incorporating risk assessment, brief advice and referral for such behavioural risks has been recommended in a number of countries [13-23].

In a range of countries including Australia, community health services represent a key primary health care setting for the provision of preventive health care [19,20,24-30]. Community health services are the second largest provider of health care to the Australian population, providing approximately 8.6 million occasions of service annually in one state alone [18,29,31]. In Australia, community health services provide a diverse range of care types, including: community nursing, allied health, community child and family health, diabetes services, aged care, post acute care, mental health, drug and alcohol, and sexual assault care; and are delivered by a variety of providers, most commonly nurses and allied health professionals [29].

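### Brief advice and referral power is called conservative because smoking is said to be the rarest risk, but the Background puts risky alcohol use lower (13% against 20%), so the group 3 figure does not carry over to alcohol

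*Protocol article*

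**What the plan says.** The Sample size section takes one limiting case for brief advice and referral across all four risks. It is "conservatively based on the expected number of smokers; as smoking is the least prevalent risk behaviour". Group 3 is used because it has the shortest follow-up, and it is expected to contain "approximately 450 (20%) smokers in the baseline period and 75 smokers during the follow-up period". From these counts the article concludes that "the study will have over 80% power to detect a 20.9% improvement in the prevalence of such care", that is, "a change from 50.0% to 70.9"%. The same figure is given for offering a referral. The significance level appears earlier in the section, in the sentence on risk assessment: "between baseline and follow-up for the three groups at the 1% significance level".

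The Background gives the only prevalence figures in the article: "20% of adults are current smokers, 13% consume alcohol at risky levels". The other risks listed there are all more common: 35% sedentary with a further 37% at low activity, 46% with inadequate fruit intake and 86% with inadequate vegetable intake.

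Under Statistical analysis (Client data), the brief advice and referral models include only clients who report the risk concerned, and change is judged for each group.

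**The concern.** The reason given for calling the calculation conservative conflicts with the article's own prevalence figures. Because the advice and referral models use only clients at risk, the prevalence of a risk sets the number analysed. A risk less common than smoking has fewer clients, and therefore less power, than the case presented as the worst.

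The primary aim covers assessment, advice and referral for each of the four risks, so advice and referral for alcohol both fall under it. A reader who relies on the Sample size section would take a null alcohol result in group 3 as coming from a comparison with over 80% power for a 20.9-point improvement. On the Background figures that is not so.

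**Working it through.** **Inputs**
- Clients per group (Clients section): "750, 1500 and 2250 clients in the baseline period for groups 1, 2 and 3 respectively, and 1875, 1125 and 375 clients" at follow-up. Group 3 therefore has 2250 at baseline and 375 at follow-up.
- Smoking 20% and risky alcohol use 13% (Background).
- Rates of 50.0% and 70.9%, and the 1% level (Sample size). Sidedness is not stated; two-sided is assumed because it reproduces the stated figure.

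**Formula** (two independent proportions, pooled variance under the null, no continuity correction)
- p̄ = (n1·p1 + n2·p2)/(n1 + n2)
- SE0 = √[p̄(1 − p̄)(1/n1 + 1/n2)]
- SE1 = √[p1(1 − p1)/n1 + p2(1 − p2)/n2]
- Power = Φ[(p2 − p1 − 2.576·SE0)/SE1]

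**Step 1: reproduce the stated figure (smokers, group 3)**
- n1 = 0.20 × 2250 = 450; n2 = 0.20 × 375 = 75.
- p̄ = 0.530, SE0 = 0.0623, SE1 = 0.0575.
- (0.209 − 2.576 × 0.0623)/0.0575 ≈ 0.846, so power is 80.1%.

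This matches the article. Other conventions do not: 76.1% with a continuity correction, 86.8% at one-sided 1%, 93.5% at two-sided 5%.

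**Step 2: the same calculation for alcohol at 13%, group 3**
- n1 = 0.13 × 2250 = 292.5; n2 = 0.13 × 375 = 48.75 (about 292 and 49).
- p̄ = 0.530, SE0 = 0.0772, SE1 = 0.0713.
- (0.209 − 2.576 × 0.0772)/0.0713 ≈ 0.142, so power is 55.6%.
- Solving for 80% power gives a detectable difference of 25.6 points (50.0% to 75.6%).

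**Step 3: alcohol at 13% in the other groups, same 20.9-point change**
- Group 1: 0.13 × 750 = 97.5 and 0.13 × 1875 = 243.75; power 85.5%.
- Group 2: 0.13 × 1500 = 195 and 0.13 × 1125 = 146.25; power 91.3%.

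**Step 4: sensitivity of group 3 to the alcohol prevalence**

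| Assumed prevalence | At risk, baseline / follow-up | Power for 50.0% to 70.9% |
|---|---|---|
| 10% | 225 / 37.5 | 41% |
| 13% | 292.5 / 48.75 | 56% |
| 15% | 337.5 / 56.25 | 64% |
| 17% | 382.5 / 63.75 | 71% |
| 20% | 450 / 75 | 80% |
| 25% | 562.5 / 93.75 | 90% |

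The stated case has almost no slack: 80.1% at exactly 20%. Any alcohol prevalence below about 20% takes group 3 under 80%.

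**The case against.** The strongest counter-argument is that the 13% may not measure what the trial will count. It is a figure for Australian adults, given without a definition. The trial classes a client as at risk for more than two standard drinks a day, or for four or more on any one occasion (Client risk status). The single-occasion criterion could lift prevalence among clients above 13%, perhaps above 20%. The two sections also cite different sources, neither of which is at hand. This stands as a limit on the size of the shortfall. It does not remove the contradiction: the Sample size section makes no such argument, and its 20% for smoking equals the Background's population figure, which makes 13% the like-for-like value for alcohol.

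Second, a reader might infer that the trial is underpowered for alcohol altogether. The documents do not support that. Groups 1 and 2 keep over 80% power at 13%, and only group 3 falls short. But group 3 is the group for which the article states its figure, and effects are judged group by group.

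Third, the 56% rests on the 50% baseline, which the article itself treats as the worst case. With the same counts and the same 20.9-point rise, power is about 86% from a 10% baseline and 97% from 3%. The Background cites one Australian study with brief advice at 2% to 3%, but another with advice or referral at 43% to 66%. From a 40% baseline power is still about 56%. So a lower baseline could rescue power in practice, but it does not rescue the claim as stated, which is made at 50%.

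**Conclusion.** The point holds, with a limited reach. The article's statement that smoking is the least prevalent of the four risks contradicts its own Background, and the description of the power calculation as conservative falls with it. On the article's figures, the group 3 claim of over 80% power for a 20.9-point improvement does not extend to brief advice or referral for alcohol: power is about 56% and the detectable improvement about 25.6 points.

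These sizes assume a 13% alcohol prevalence among clients, a 50% baseline, a two-sided 1% test and a simple comparison of two proportions. It would go too far to say that power for alcohol definitely fails. No prevalence under the trial's alcohol definition is given, and at about 20% or more the stated figure stands. Design, recruitment and analysis are unaffected, so this is something that should be fixed in the text rather than a fault in the trial.

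**What to change.** In the Sample size section, delete the word conservatively and the clause naming smoking as the rarest risk, and label the 20.9-point figure as applying to smoking and the more prevalent risks. Then do one of two things:
- state the alcohol case for group 3 together with its assumed prevalence (at 13%: about 292 and 49 clients, 50.0% to 75.6% detectable with 80% power at two-sided 1%); or
- give an alcohol prevalence under the trial's own definition that supports 20% or more, and keep the 20.9-point figure for all four risks.

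The second is preferable if such a figure exists, because the 13% may not match the trial's definition. The cost is rewording and, under the first option, a less favourable stated figure for alcohol in group 3. No extra clients are needed.
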